## Abstract

The malaria parasite *Plasmodium falciparum* (*Pf*) can sequester in the placenta resulting in low density of peripheral parasitemia and consequently in false negative malaria diagnosis (by microscopy) in pregnant women. Moreover, the use of rapid diagnostic tests (RDTs) in diagnostic strategies, including those for the detection of a malaria infection during pregnancy, is constrained by either persistent malaria antigen (histidine-rich protein 2; HRP2) after successful treatment, leading to false positive test results, or by false negative results as previously mentioned due to parasite sequestration (which is further exacerbated due to the low limited of detection [LoD] of conventional RDTs) or to HRP2 deletion. Recently, a direct blood polymerase chain reaction combined with a nucleic acid lateral flow immunoassay (dbPCR-NALFIA) has been developed, which circumvents these challenges and has demonstrated its diagnostic potential in phase 1 and 2 studies. The PREG-DIAGMAL trial presented in this manuscript will assess the diagnostic performance of dbPCR-NALFIA for the diagnostic of malaria in pregnant women and its potential to monitor treatment efficacy in these subjects. The work is ancillary embedded in an ongoing EDCTP funded trial, the PyraPreg project (PACTR202011812241529) in which the safety and efficacy of a newly registered Artemisinin-Based Combination (Pyronaridine-Artesunate) is being evaluated in pregnant women. This is a Phase 3 diagnostic evaluation conducted in 2 African countries: Democratic Republic of the Congo (DRC) and Burkina Faso. Pregnant women fulfilling the inclusion criteria of the PyraPreg study will be also invited to participate in the PREG-DIAGMAL study. Diagnostic accuracy will be assessed following the WHO/TDR guidelines for the evaluation of diagnostics and reported according to STARD principles. Due to the lack of a 100% specific and sensitive standard diagnostic test for malaria, the sensitivity and specificity of the new test will be compared to the available diagnostic practice in place at the selected settings (microscopy and/or RDT) and to quantitative PCR as the reference test. This phase 3 diagnostic study is designed towards the evaluation of the performance of a new diagnostic tool for the screening of malaria and the monitoring of treatment in pregnant women under real conditions life. If successful, the dbPCR-NALFIA could be a valuable tool to add to the diagnostic arsenal for malaria, in particular during pregnancy. Trial registration: Pan African Clinical Trial Registry database (PACTR202203780981413). Registered on 17 March 2022.

## 1. Background

Malaria in humans is a life-threatening disease caused by single-cell (protozoan) parasites of the genus *Plasmodium*: *P. falciparum*, *P. vivax*, *P. ovale*, *P. malariae,* and *P. knowlesi*. Malaria is a major public health problem in (sub-) tropical regions with approximately half of the world’s population being at risk. In 2019, about 229 million clinical malaria cases and nearly 409,000 deaths were reported worldwide. The majority of the cases (94%) occurred in sub-Saharan Africa, with young children and pregnant women being most at risk [1]. Malaria management has been greatly improved due to the wide implementation of World Health Organization (WHO) recommendations that all suspected malaria cases should have a parasite-based diagnosis prior to initiating treatment with artemisinin-based combination therapy (ACT) [2]. Malaria parasite specific antigen-detecting Rapid Diagnostic Tests (RDTs) are considered as appropriate tools to manage febrile illnesses in malaria endemic settings [1]. The short time needed to obtain a diagnostic result, simple read-out, easy performance by non-technical staff, and relatively low costs have contributed to the acceptance of RDTs in differentiating malaria from other causes of fever [3]. Most commonly used RDTs are the *P. falciparum* histidine-rich protein 2 (*Pf*HRP2) based RDT, specific for *P. falciparum* only, and the *Plasmodium* lactate dehydrogenase (*p*LDH)-based RDT that detects all *Plasmodium* species, or combination tests with two test lines (a *P. falciparum*-specific line and an all *Plasmodium*-test line) [4,5].

However, the success of RDTs’ implementation is constrained by persisting *Pf*HRP2 after successful treatment, which may lead to false positive test results [6,7,8]. Furthermore, studies report false positive diagnoses by *Pf*HRP2-based RDT particularly in seasonal malaria transmission settings or under harsh environmental conditions [9,10]. Of greater concern are false negative *Pf*HRP2-RDT results increasingly reported from malaria endemic regions due to *hrp*2 deletions in the *Plasmodium* genome [11,12,13]. In these settings, a HRP2-based RDT will be negative, even if a *P. falciparum* infection is present. Finally, RDTs (*p*LDH-based in particular) have sensitivity limitations, also resulting in false negative results [5,14]. This is particularly evident in the case of pregnant women where the malaria parasites, in particular *P. falciparum¸* sequester in the placenta (placental malaria). Consequently, in pregnant women, peripheral parasitaemia can be absent or below the detection limit of RDTs [15,16].

Although malaria microscopy remains the standard for clinical diagnotis, the limit of detection (LoD) of malaria parasites by expert microscopy (around 10 parasites/μL) could miss low parasitaemia. Furthermore, the LoD depends on the microscopic reading technique, the experience of the reader, and the availability of a well-maintained microscope [17]. 

In this context, there is a pressing need to develop more sensitive and accurate malaria diagnostic tests that circumvent the limitations of RDTs and microscopy. In general, molecular biology-based diagnostic tests are considered to be the best methods to detect malaria infections, irrespective of low parasite densities or HRP2 deletions [18,19,20]. Several molecular methods have been developed, including conventional and quantitative real-time polymerase chain reaction (qPCR), nucleic acid sequence-based amplification, or loop mediated amplification [19]. These platforms are highly sensitive and can allow species differentiation and parasite quantification. These formats would be ideal for patient management, but their relative complexity hampers their use as near point of care (PoC) tests. In particular samples’ processing (DNA extraction), and complicated read-out systems (gel electrophoresis with UV reading or computerised systems) hamper wide implementation [19].

To circumvent these challenges, a simple molecular diagnostic platform to diagnose malaria has been developed that can be used near patient (PoC). This platform combines direct-on-blood (db)PCR with a nucleic acid lateral flow immunoassay (NALFIA) to detect *Plasmodium* species in a multiplex format [21]. The NALFIA is a simple read-out system, comparable to a dipstick, to visualize amplicons. The dbPCR-NALFIA system has an analytic sensitivity of 1.0 to 0.1 parasite/µL of blood (10–100 times more sensitive than conventional malaria diagnostics) with a high sensitivity and specificity in clinical settings [21]. Importantly, the platform allows for direct amplification of *Plasmodium* DNA in whole blood [22] by utilizing specific enzymes and buffers that are able to withstand the inhibitory effects usually encountered when directly amplifying DNA in blood. This avoids contamination-prone and labour-intensive parasite DNA extraction from a clinical sample. This dbPCR-NALFIA has passed laboratory evaluations and trials in disease endemic countries [22,23]. Recently the dbPCR-NALFIA has been optimised by using a mini-PCR system (battery operated, reducing its dependency on electricity, solar powered and controlled via an application on a mobile telephone) thereby enhancing its field applicability. Currently, the platform (mini-dbPCR-NALFIA) is undergoing phase III diagnostic evaluations in the framework of the European & Developing Countries Clinical Trials Partnership (EDCTP) funded DIAGMAL project (PACTR202202766889963 and ISRCTN13334317) in 5 African countries: Ethiopia, Burkina Faso, Namibia, Sudan, and Kenya. In this project, the diagnostic performance of the mini-dbPCR-NALFIA test will be evaluated in the context of different malaria epidemiology settings. Furthermore, a cost effectiveness evaluation of the implementation of this new diagnostic platform will be performed in the framework of this study.

These above-mentioned evaluations do not include pregnant women who are however very vulnerable to malaria infections [24,25]. Indeed, *P. falciparum* can sequester in the placenta during pregnancy, resulting in low peripheral parasitemia. Consequently, malaria diagnostic tests are often false negative in pregnant women who actually do have a *P. falciparum* malaria infection [26,27] and they do not receive adequate treatment. Due to its very high analytical sensitivity, the mini-dbPCR-NALFIA test could be a good diagnostic test to properly detect malaria in pregnancy (MiP). 

In addition, the treatment of malaria in pregnancy needs to be safe and efficient. Currently most cases of MiP are treated with ACT [24,28]. It is however difficult to measure the effect of treatment in these specific cases. The mini-dbPCR-NALFIA might provide a suitable platform to follow treatment efficacy as well.

The main aim of the study is to evaluate the diagnostic performance of the mini-dbPCR-NALFIA test for MiP. In order to achieve that, the following study objectives will be achieved through a dedicated diagnostic trial focussing on malaria infection in pregnant women.

The planned work has the following primary objective: to assess the diagnostic accuracy of the mini-dbPCR-NALFIA test for the diagnosis of malaria in pregnancy compared to routine diagnostic procedure(s) in place (microscopy and/or RDTs) and qPCR (as reference test). The secondary objectives of the trial are:

To determine the utility of the mini-dbPCR-NALFIA to monitor anti-malaria treatment with ACT efficacy in pregnancy during a follow-up period of 63 days.

## 2. Design/Methods

The trial design is presented below by following the SPIRIT guidelines. This trial is an ancillary study embedded in an EDCTP funded drug trial (Safety and Efficacy of a newly registered Artemisinin-Based Combination (Pyronaridine-Artesunate-PYRAMAX^®^) (PyraPreg [PACTR202011812241529]). The planned phase 3 diagnostic study consists of two components.

The first component will assess the diagnostic accuracy of the mini-dbPCR-NALFIA test for the diagnosis of malaria in pregnant women (**diagnostic screening part**). The study hypothesis for this component is: “mini-dbPCR-NALFIA will offer an improved diagnostic platform over microscopy and/or currently available RDTs for the detection of malaria infection in pregnant women”. This will be studied through a phase 3 diagnostic trial. Diagnostic performance will be assessed following the WHO/TDR guidelines for the evaluation of diagnostics [29] and the results will be reported according to STARD principles [30]. This phase 3 evaluation will screen pregnant women at the point of enrolment for the main PyraPreg trial for the presence of malaria in both Burkina Faso and DRC. Potential study participants (≥15 years of age, pregnant, able to provide informed consent) will be identified during their visits to the study health facility and asked to participate in the diagnostic study. Consequently, both malaria negative, as well as malaria positive (confirmed by the standard diagnostic practices in place), will be tested for this screening part of the study. An additional blood sample (finger prick blood), next to the clinical sampling performed in the framework of the PyraPreg project at the point of screening, will be collected from the same women. This sample will be analysed by mini-dbPCR-NALFIA (index test) and qPCR (as reference test). The results of the experimental diagnostic testing will not be used to make any decisions about the clinical management of pregnant women.

For the **treatment follow-up part** (second component), we will recruit the same women who have been recruited for the main PyraPreg trial (in Burkina Faso only) and who will be followed up for a period of 63 days. At each of their planned study visit (at days 1, 2, 3, 7, 14, 21, 28, 35, 42, 49-56, and 63) we will obtain an additional blood sample for qPCR and mini-dbPCR-NALFIA testing.

### 2.1. Methods: Participants, Test evaluation and Outcomes

#### 2.1.1. Study Sites

The study will be carried out in 2 African countries (Burkina Faso and DRC).

In Burkina Faso, the study will be conducted by the Clinical Research Unit of Nanoro (CRUN), located in central—west Burkina Faso, approximately 90 Km from the capital city, Ouagadougou. Malaria is the main public health problem and represents a significant burden, particularly for pregnant women and children. The prevalence of malaria in pregnancy is estimated to be around 25% in the region.

In DRC, the study will be conducted by the Department of Tropical Medicine, UNIKIN. Participants will be recruited in the Kinshasa suburb, where malaria transmission is perennial and the prevalence is estimated at around 30%. 

#### 2.1.2. Eligibility Criteria

The screening study will include cases who fulfil the following inclusion criteria:Gestation ≥16 weeks and <37 weeks as assessed by ultrasound (if possible) or uterine height or late menstrual period;Age: ≥15 years;Residence within the health facility catchment area;Ability to provide written informed consent.

The treatment follow-up study will include cases that have met the inclusion criteria for the PyraPreg study. These have been defined as follows:Gestation ≥16 weeks and <37 weeks as assessed by ultrasound (if possible,) or uterine height or late menstrual period;*P. falciparum* mono-infection (by microscopy) of any density, regardless of symptoms and HIV status;Haemoglobin ≥7 g/dL;Age: ≥15 years;Residence within the health facility catchment area;Willing to adhere to study requirements and to deliver at the health facility;Ability to provide written informed consent.

Not meeting the inclusion criteria will result in exclusion from the study.

#### 2.1.3. Who will Take Informed Consent?

Written informed consent will be obtained from all the study participants before enrolment. After an interview with the study physician or a member of the study research team, a potential participant will be asked to document her consent by signing an informed consent form. If the participant is a minor (according to the applicable national law), the consent will be signed by a parent or a legal guardian. Nevertheless, an informed assent form must be signed by the minor participant. The signed informed consent (or thumb printed whenever the patient or the parents/guardians are illiterate) must be obtained before any blood sample or tests related to the study are carried out.

#### 2.1.4. Additional Consent Provisions for Collection and Use of Participant Data and Biological Specimens

During the informed consent procedure, study participants (and/or parents/guardians) will be informed about future investigations on the collected blood samples. They will be explained that future investigations will only focus on the understanding of the performance and quality of diagnostic procedures. For this purpose, part of the collected biological specimens may be transported and tested in Amsterdam (The Netherlands). No genetic testing on the human host will be performed.

### 2.2. Interventions

#### 2.2.1. Explanation of the Choice of Comparator

The diagnostic performance of the mini-dbPCR-NALFIA for the screening of malaria and the follow-up of malaria treatment in pregnant women will be compared to the standard malaria diagnostic practices in place in the 2 participating countries (i.e., microscopy and/or rapid diagnostic test). Established qPCR will be used as the reference standard.

#### 2.2.2. Intervention

Both RDT and/or microscopy will be performed as part of the routine diagnostic procedures in place at the study sites. RDT will be performed according to the manufacturer procedures. Thin and thick blood films will be prepared and Giemsa stained. Blood slides will be independently read by 2 expert microscopists. Parasite density will be calculated by counting the number of asexual parasites per 500 leukocytes in the thick blood film, based on an assumed WBC of 8000/µL by light microscopy at 1000× magnification. In addition to routine diagnostic procedures in place, an additional blood sample (preferably finger prick blood) will be collected for test evaluation (index and reference tests). Blood samples will be properly labelled with patients’ initials, inclusion number, protocol number, scheduled study visit, and the date of the sampling. For the index test (mini-dbPCR-NALFIA) <20 μL of blood (collected in an EDTA tube) is needed. For reference testing (qPCR), three blood spots will be collected on Whatman 3 filter paper [31]; one sample for qPCR, the second and third sample for QC procedures (10%) or back-up.

#### 2.2.3. Criteria for Discontinuing or Modifying Allocated Interventions

Only a single additional blood sample will be collected for the screening study. Repeated sampling is needed for the follow-up study but will always involve a single blood sample at the time of follow-up. Treatment decisions will be made on the basis of the PyraPreg study. There will be no interference with standard practices. There is no need to define criteria for discontinuing or modifying the interventions.

#### 2.2.4. Strategies to Improve Adhesion to Intervention

The study is an ancillary study embedded in the PyraPreg trial and has the same sampling points as defined in the PyraPreg trial (day of screening and followed by days 1, 2, 3, 7, 14, 21, 28, 35, 42, 49–56 and 63 for treatment follow-up) and adherence strategy has been developed for PyraPreg trial. Consequently, there is no need to design new strategies to improve adherence to interventions.

#### 2.2.5. Relevant Concomitant Care Permitted or Prohibited during the Trial

Not applicable, as this is a diagnostic study. Prior use of antimalarial drugs might influence diagnostic test performance and then prior drug use in the past 14 days preceding blood collection will be recorded.

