#### 2.2.7. Outcomes

The outcome (for the diagnostic screening and treatment follow-up parts) will be reported according to STARD principles [30]. We will report sensitivity, specificity, negative, and positive predictive values (primary outcome) of the mini-dbPCR-NALFIA test. The outcomes of the evaluations will be further analysed using 2 × 2 tables (at 95% confidence intervals), and comparisons of the performance of the diagnostic test under investigation will be made with standard diagnostic procedures in place and qPCR as the accepted reference test to determine the agreement between different tests (expressed as kappa values) [29]. 

To determine the utility of the mini-dbPCR-NALFIA test in monitoring treatment efficacy, parasite clearance will be assessed by mini-dbPCR-NALFIA and compared with qPCR. 

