### 2.6. Statistical Methods

#### 2.6.1. Statistical Methods for Primary and Secondary Outcomes

As mentioned above, the outcomes of the evaluations will be analysed using 2 × 2 tables (at 95% confidence intervals), and comparisons will be made with standard diagnostic procedures in place and qPCR as the accepted reference test. Positive and Negative Predictive Values will be calculated. The sensitivity and specificity of the mini-dbPCR-NALFIA are assumed to be at least 90% [23]. The utility of the mini-dbPCR-NALFIA to monitor treatment success (in terms of recurrent parasitemia) will be compared to qPCR. The association between the molecular test results obtained during the follow-up will be assessed using logistic regression models.

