#### 2.6.3. Methods for Additional Analyses (e.g., Subgroup Analyses)

Not applicable.

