## 3. Discussion

Pregnant women require specific consideration in malaria control programs in endemic countries. Indeed, the increasing susceptibility to malaria infection during pregnancy, makes pregnant women living in endemic areas, an important reservoir of *Plasmodium* in the community [33]. The high susceptibility of pregnant women in many endemic countries interferes with diagnostic testing during pregnancy, rending target interventions ineffective for control [34]. This situation becomes exacerbated when available diagnostics have a low detection limit [6,7,8,9,10] and are unable to detect low peripheral parasitemia due to the sequestration of the parasite in the placenta [35]. Although microscopy is still considered to be the reference test for the diagnostic of malaria, despite the limit of detection [17], it is unfortunately not readily available in rural areas for reasons such as the lack of qualified staff and sufficient laboratory infrastructure. This is also the case for molecular biology for which specific equipment and highly trained technicians are needed in order to be adequately performed [19]. In order to propose an alternative diagnostic tool for the correct diagnosis of malaria in endemic areas particularly in pregnant women and where suitable laboratory facilities are lacking, an innovative diagnostic platform combining direct blood amplification in a miniaturized PCR system with NALFIA as a read-out to diagnose *Plasmodium* infections in a multiplex format has been developed.

The present trial has been designed to assess the diagnostic performance of this platform for the detection of *Plasmodium* species in pregnant women during antenatal consultation and treatment follow-up. The proposed trial will validate the anticipated low limit of detection and sensitivity and specificity of the new diagnostic platform. If these diagnostic parameters are achieved, this study will provide the evidence needed for the introduction of the mini-dbPCR-NALFIA in the routine health system for a correct diagnosis of malaria and treatment follow-up during pregnancy.

**Trial status:** This is the protocol Version 2.0, of 11 March 2021. Ethical approvals have been obtained for both participating countries. At the time of this manuscript submission, study participants’ enrollment has started in Burkina Faso (8 November 2021), and in DRC (7 December 2021). The trial is ongoing with an anticipated completion date in December 2023.

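### Section 2.6.3 declares additional analyses not applicable, leaving the promised detection-limit validation and the recorded antimalarial use without an analysis, and no analysis by country is stated for PPV and NPV

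*Protocol article*

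**What the plan says.** The section whose heading begins "Methods for Additional Analyses (e.g., Subgroup Analyses" (2.6.3) contains only the statement that this is not applicable.

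Other parts of the protocol article bear on it:

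- **Detection limit.** The Discussion states: "The proposed trial will validate the anticipated low limit of detection and sensitivity and specificity of the new diagnostic platform". It adds that, if these parameters are achieved, the study will supply the evidence for routine introduction. The Background gives the anticipated value: the system "has an analytic sensitivity of 1.0 to 0.1 parasite/µL of blood".
- **Prior antimalarials.** Section 2.2.5 gives a reason for collecting the variable: "Prior use of antimalarial drugs might influence diagnostic test performance and then prior drug use in the past 14 days" before blood collection is to be recorded.
- **Predictive values.** Section 2.2.7 makes them primary: "We will report sensitivity, specificity, negative, and positive predictive values (primary outcome) of the mini-dbPCR-NALFIA test". Section 2.6.1 adds only "Positive and Negative Predictive Values will be calculated". Neither mentions country.
- **Prevalence.** Section 2.1.1 says of the Burkina Faso site "The prevalence of malaria in pregnancy is estimated to be around 25% in the region", and of the Kinshasa site that "malaria transmission is perennial and the prevalence is estimated at around 30" percent. The second figure is not said to refer to pregnancy.

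**The concern.** An explicit declaration that additional analyses do not apply is a position taken. It is not a detail left to a later analysis plan.

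The detection-limit promise is the most serious of the three points. The test is motivated by low-density infection caused by placental sequestration. Expert microscopy is said in the Background to reach about 10 parasites/µL, and the new test is expected to go 10 to 100 times lower. An overall sensitivity averages over easy and hard infections and says nothing about the density at which detection fails. If the plan is followed as written, the Discussion's conclusion has no analysis behind it.

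Prior antimalarial use is collected for one named purpose, and the natural way of serving that purpose is then ruled out. The predictive values will be read by two countries whose prevalence may differ. If strata and density cut-points are chosen only once the data are in hand, they will be open to the charge of selection.

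**Working it through.** **1. Is there a density-based analysis?** Sections 2.2.7 and 2.6.1 list sensitivity, specificity, PPV, NPV, 2 × 2 tables with 95% intervals, kappa, a comparison of clearance and recurrence with qPCR, and a logistic regression relating the molecular results during follow-up. None is stated to use parasite density. A 2 × 2 table against a positive/negative reference yields no detection limit.

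**2. Is there an analysis that uses prior antimalarials?** None in Sections 2.2.7, 2.6.1 or 2.6.3.

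**3. What the sample size was built for.** Section 2.2.9 gives the half-width formula 1.96 × √[p(1 − p)/n], a prevalence of 25% and a total of 555. It does not state the half-width. With p = 0.90 (Section 2.6.1) and an assumed half-width of 0.05:

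- n = 1.96² × 0.90 × 0.10 / 0.05² = 138.3, rounded up to 139 infected women
- N = 138.3 / 0.25 = 553.2, or 139 / 0.25 = 556

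This reproduces 555 closely; half-widths of 0.04 and 0.06 give 868 and 388. So 555 fits one overall sensitivity estimate at the Nanoro prevalence, with no allowance for strata.

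**4. Predictive values at the two prevalences** (sensitivity = specificity = 0.90):

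- PPV = 0.9π / [0.9π + 0.1(1 − π)]
- NPV = 0.9(1 − π) / [0.9(1 − π) + 0.1π]

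| Prevalence π | PPV | NPV |
|---|---|---|
| 25% | 0.225/0.300 = 75.0% | 0.675/0.700 = 96.4% |
| 30% | 0.270/0.340 = 79.4% | 0.630/0.660 = 95.5% |

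The shift is 4.4 points for PPV and 1.0 for NPV. At 95%/95%, PPV is 86.4% against 89.1% and NPV 98.3% against 97.8%.

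For scale, an overall PPV at 27.5% prevalence (an assumed equal split) rests on about 178 test positives. Its half-width is 1.96 × √(0.773 × 0.227/178) ≈ 0.062. The country shift in PPV is smaller than that.

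**5. Precision by country** (assumed equal split, 277.5 women each):

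- Burkina Faso: 0.25 × 277.5 = 69.4 infected; half-width 1.96 × √(0.09/69.4) = 7.1 points
- DRC: 0.30 × 277.5 = 83.3 infected; half-width 6.4 points

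The overall figure is 5.0 points.

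**6. Precision around prior antimalarial use** (share f of recent users assumed; infected women overall 0.25 × 555 = 138.75; p = 0.90):

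| f | Infected recent users | Half-width among them | Infected women left after exclusion | Half-width after exclusion |
|---|---|---|---|---|
| 5% | 6.9 | 22 points | 131.8 | 5.1 points |
| 10% | 13.9 | 16 points | 124.9 | 5.3 points |
| 20% | 27.8 | 11 points | 111.0 | 5.6 points |
| 30% | 41.6 | 9 points | 97.1 | 6.0 points |

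The normal approximation is rough at the smallest counts. Estimating accuracy among recent users would be imprecise, while repeating the main analysis without them costs little precision.

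**The case against.** The best counter-case has four parts.

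- **The detection-limit sentence appears once, in the Discussion.** It is neither an objective nor an outcome, and the Background presents the figure as already established analytically. That is fair, and it makes softening the sentence a legitimate repair. The mismatch remains until one side is changed.
- **It is unclear that qPCR density will be available.** The specimen paragraph at the end of Section 2.5.4 limits the PCR work to whether *Plasmodium* is present, and the only density the article describes (Section 2.2.2) comes from microscopy. This stands as an ambiguity. That paragraph chiefly excludes human genetic analysis, the Abstract names quantitative PCR as the reference, and the Background says molecular platforms can quantify parasites. The article should settle it.
- **Recording a covariate without naming its analysis is common in an article.** This is correct, and Section 2.2.5 is not in strict contradiction with Section 2.6.3. What remains is a gap between the reason given for collecting the variable and the analyses stated.
- **Pooling across countries is not stated.** A reader might infer it from the single total of 555, the single set of predictive values and the entry in Section 2.6.3. No section says so. The Kinshasa prevalence may not be comparable, and the effect is modest in any case.

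Two further readings are tempting and unsupported. One is that every planned analysis is a yes/no table; kappa, the clearance comparison and the logistic regression show otherwise. The other is that the plan would read as successful while missing low-density infections. With an invented mix of 60% higher-density infections detected at 99% and 40% lower-density infections detected at 76%, overall sensitivity is 0.6 × 0.99 + 0.4 × 0.76 = 89.8%. That shows how an average can hide weak detection, but the mix comes from no document. The result falls just under 90%, and Section 2.6.1 gives 90% as an assumption, not a success criterion.

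**Conclusion.** The point holds in a limited form and should be corrected before the data are analysed.

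- **Detection limit:** the stated analyses cannot support the Discussion's claim. This follows from the text and needs no assumption.
- **Prior antimalarials:** a variable recorded because it might affect test performance has no stated use. This is a gap in the plan, not a contradiction.
- **Country:** no analysis by country is stated for prevalence-dependent primary outcomes. The size is modest, 4.4 points of PPV and 1.0 point of NPV at 90%/90%, and it assumes that the quoted prevalences apply to the women screened.

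The overall sensitivity and specificity estimates remain valid as planned. The precision figures rest on an assumed ±5-point target, an assumed equal country split and assumed prior use of 5 to 30%.

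**What to change.** Replace the entry in Section 2.6.3 with three prespecified analyses, labelled as estimation and not as tests:

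1. **Detection by density.** Index-test positivity by qPCR-derived parasite density, in bands fixed in advance and as a logistic or probit curve on log density. Amend the specimen paragraph in Section 2.5.4 to say that qPCR density will be reported. If qPCR will be read only as positive or negative, delete the detection-limit claim from the Discussion instead.
2. **Prior antimalarials.** Repeat the primary accuracy analysis excluding women with antimalarial use in the 14 days before sampling.
3. **Country.** Report PPV and NPV by country alongside any overall figure.

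The cost is a few more tables and wider intervals, since 555 does not size strata: about ±6 to 7 points for sensitivity by country, and about ±5 to 6 points after excluding recent users, under the assumptions above. Items 2 and 3 use data the plan already collects. Item 1 needs no extra sampling, but depends on qPCR density being recorded.
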